##### Text/Email Messages

A total of 4 messages were delivered to experimental group children each week (total of 23 messages throughout intervention). Messages included announcing the release of a new chapter by a comic character (see Figure 5, left), a reminder to read the comic, and a reminder to select a goal for each week. Messages were delivered via text and/or email based on participant preference identified during the baseline visit.

#### Parent/Guardian Components

##### Newsletters

Parents/guardians in the experimental group received 6 Web-based newsletters with similar health messages as their child (see Figure 6, left). Newsletter content comprised healthy recipes, healthy feedings tips for the family, links to coupons to support healthy eating, and links to fun community events (eg, fall and winter festivals). In addition, they were given access to the “Game On” comic and character profiles. Newsletters were translated into Spanish and provided to those parents who expressed a preference for Spanish-language materials.

##### Text/Email Messages

A total of 2 messages were delivered to experimental group parents/guardians (total of 11 messages throughout intervention) each week. Parents/guardians received messages announcing the release of a new newsletter. In addition, they received reminders to encourage their child to read the comic. Messages were delivered via text and/or email based on participant preference identified during baseline. Messages were translated into Spanish and provided to those parents who expressed a preference for Spanish-language materials.

### Comparison Group Description

The comparison group had access to Web-based tools similarly hosted on a password-protected website and optimized for use on tablet devices and touch-screen computer/laptop devices. All study participants received training on how to use the website at baseline.

**Figure 4 figure4:**
[figure not shown]
Experimental group (child) goal-setting component (top) with link in the character message at the end of each comic chapter (top left), list of goals (top center), and goal-specific tip (top right) and comparison group (child) goal-setting component (bottom) with link in the Web-based newsletter (bottom left), list of goals (bottom center), and goal-specific tip (bottom right).

#### Child Components

##### Newsletters

Children randomized to the comparison group received 6 Web-based newsletters with F/V or water information (see Figure 3, right). Similar to the comic, newsletter content was tailored (to include more information related to either F/V or water) based on responses to initial screening questions at baseline related to child F/V and water intake, child self-efficacy to increase F/V and water intake, and parent self-efficacy to support the child in increasing F/V and water intake. Newsletters were housed on a home page, and one was made available at the beginning of each week for 6 weeks. Health-related content for the comparison group was similar to that for the experimental group but was presented in a newsletter (didactic) format. The content comprised healthy eating tips, healthy recipes, diet-related knowledge/facts, health-promoting online games, and a link to selected weekly goals. Of note, comparison group participants were provided access to the “Game On” comic on completion of all data collection in April 2018.

##### Goal Setting and Assessment

Similar to children in the experimental group, children in the comparison group also had a goal-setting component (see Figure 4, bottom), wherein each week, the child could click the weekly goal link in the newsletter (see Figure 4, bottom left); select from 8 tailored goals to work on, related to either encouraging increased F/V or water intake (see Figure 4, bottom center); receive a tailored tip to provide assistance in achieving that specific goal throughout the week (see Figure 4, bottom right); and self-assess at the end of the week on how they did on the goal over the past week and receive feedback/encouragement. Unlike the goal-setting component in the experimental group, the format in which the goal setting was conducted in the comparison group was non-narrative.

**Figure 5 figure5:**
[figure not shown]
Examples of text messages sent to children in the experimental group (left) and comparison group (right).

##### Text/Email Messages

A total of 3 messages were delivered to comparison group children each week (total of 17 messages throughout intervention). Messages included announcing the release of a new newsletter, a reminder to read the newsletter, and a reminder to select a goal for each week (see Figure 5, right). Messages were delivered via text and/or email based on participant preference identified during the baseline visit.

#### Parent/Guardian Components

##### Newsletters

Parents/guardians of the comparison group received the same 6 Web-based newsletters (in English or Spanish) as that of the parents/guardians in the experimental group. However, parents/guardians in the comparison group were not given access to the “Game On” comic and character profiles (see Figure 6, right).

##### Text/Email Messages

One message (in English or Spanish) was delivered to comparison group parents/guardians (6 messages throughout intervention) each week announcing the release of a new newsletter. Messages were delivered via text and/or email based on participant preference identified during baseline.

### Measures

The measures collected are described in Table 2.

#### Feasibility/Acceptability Measures (Primary Measures)

##### Usage of Web-Based Tool

A custom-built platform was created to automatically log child and parent user details (created at baseline) and usage details (over 6 weeks of the intervention). User details included username, user type (parent or child), study group (experimental or comparison), type of tailored content (F/V or water), user language (English or Spanish), user email address, user mobile phone number, and start date/time (when username was created at baseline). Usage details included week number of intervention, link clicked, click time, platform used (eg, Mac OS, iPhone OS, Windows 7), and browser used and version (eg, Chrome 38.0, Safari 11.0). For child participants, additional usage data related to goal setting included weekly goal selected, date/time the goal was selected, evaluation at the end of the week (ie, “How often did you do this in the last week?”—Never, Sometimes, Most of the Time, All the Time), and date/time the goal was evaluated.

**Figure 6 figure6:**
[figure not shown]
Examples of Web-based newsletters sent to parents in the experimental group (left) and comparison group (right).

##### Usability of Web-Based Tool

Questionnaires were administered to the child and parent at several time points throughout the study. Usability was assessed with an adapted version of the System Usability Scale (SUS) [62]; Usefulness, Satisfaction, and Ease-of-use questionnaire (USE) [63]; and a 26-item acceptability/usability measure by Ben-Zeev et al [64] to assess 5 usability domains: usability, usefulness, ease of use, ease of learning, and satisfaction. The child’s questionnaire comprised 30 usability questions—10 questions from SUS, 15 from USE, and 5 from the acceptability/usability measure. On the basis of pilot testing with Latino and black children, modifications were made to tailor the questionnaire according to the literacy levels of our intended population. For example, the item “I found the system very cumbersome to use” was replaced with “I found it awkward to use” and “I would imagine most people would learn to use this system very quickly” was changed to “I think most people my age would learn to use it very quickly.” The parent questionnaire comprised 9 usability questions—2 questions from SUS, 3 questions from USE, and 4 questions from the acceptability/usability measure. On the basis of pilot testing, 1 item was modified. Similar to the child questionnaire, the item “I found the system very cumbersome to use” was replaced with “I found it awkward to use.” As the content of the parent component was presented in a more didactic format compared with that of the child component, fewer usability questions were relevant to include in the parent questionnaire. In addition, usability data in the form of qualitative interviews with child participants (at T2, T3, and T4) and parent participants (at T3 and T4) were collected to supplement quantitative usage and usability questionnaire data.

**Table 2 table2:** Key measures, data source, and time of assessment. All questionnaire items were either taken from or directly informed by validated questionnaires.

Measures		Data source	Time points				
			T1^a^	T2^b^	T3^c^	T4^d^	O^e^
**Feasibility/acceptability measures (primary measures)**							
	Usage of Web-based tool	Tracking system (internally created)	—^f^	—	—	—	C^g^/P^h^
	Usability of Web-based tool	Interview, questionnaire items [62-64]	—	C	C/P	C/P	—
	Feasibility of study implementation	Process data (eg, recruitment, attrition) [65,66]	—	—	—	C/P	S^i^
**Outcome measures (secondary measures)**							
	Dietary knowledge and attitudes	Questionnaire items [67,68]	C	C	C	C	—
	Dietary intake	Questionnaire items [69,70]	C	C	C	C	—
	Anthropometric measures	Digital stadiometer, body composition monitor	C	—	—	C	—
	Feeding practices	Questionnaire items [71]	P	—	P	P	—
	Home food environment	Questionnaire items [72]	P	—	P	P	—

^a^T1: Time points indicated by baseline.

^b^T2: Time points indicated by midpoint (3 weeks postbaseline).

^c^T3: Time points indicated by endpoint (6 weeks postbaseline).

^d^T4: Time points indicated by follow-up (3 months postintervention).

^e^O: Ongoing throughout intervention period.

^f^Indicates measures that were not collected at specific timepoints.

^g^C: Data collected from child.

^h^P: Data collected from parent/guardian.

^i^S: Data collected from study staff (internal).

##### Feasibility of Study Implementation

Process data collected throughout the study assessed the feasibility of implementing the study [65,66]. These data included quantitative/qualitative measures of recruitment and retention (ie, enrollment rate, restrictiveness of eligibility criteria, attrition rate), assessment of resource capacity (ie, staff hours needed for recruitment, participant communication approaches), data collection (ie, length of time to complete online questionnaires), and data reliability (ie, study staff adherence to protocol). Satisfaction with study participation was assessed through questionnaire items with child and parent participants at T4 (ie, frequency and format of communication and study visit scheduling with study staff) as well as qualitative observations of child participants at T1 and T4 while completing questionnaires (ie, verbal and nonverbal expressions indicating frustration, boredom, and confusion).

#### Outcome Measures (Secondary Measures)

##### Child Dietary Knowledge and Attitudes

Child participants completed a questionnaire related to knowledge, outcome expectations, self-efficacy, behavioral intention, attitudes and preferences regarding behaviors associated with F/V, water, junk food, and sugary drinks. A total of 6 questions addressed knowledge (ie, I should eat 1 cup of fruit each day for good health), 20 questions addressed outcome expectancies (ie, Eating vegetables every day will keep me from getting sick), 9 questions addressed self-efficacy (ie, If I decide to not eat junk food every day, I can do it), 10 questions addressed intention (ie, If my parent offers me water, I will drink it), 15 questions addressed attitudes (ie, I think sugary drinks are cool), and 24 questions addressed preferences (ie, Which of the following fruits do you like or dislike?). A total of 84 questions were informed by and modified from the validated ProChildren questionnaire [67] and the validated Reynolds questionnaire [68]. Modifications to wording were made to ensure questions were appropriate for this study and to adjust for literacy levels of our intended population. A recent study conducted among Latino children also adapted the ProChildren questionnaire to measure children’s self-efficacy for eating fruits and vegetables and for consuming water [73].

##### Child Dietary Intake

Child participants completed a questionnaire that assessed the frequency of consumption of F/V, water, junk food, and sugary drinks during the past 7 days. This 17-item questionnaire comprised 8 questions (6 directly from and 2 informed by) from the validated 2017 Youth Risk Behavior Surveillance System (YRBSS) questionnaire [69], which was created to monitor obesity prevalence and related behaviors, among other priority adolescent health issues. Nationally representative samples of students along with selected large urban school districts are engaged in the data collection process. Other studies conducted specifically with black and Latino children exploring dietary and physical activity behaviors have also utilized items from the YRBSS questionnaire [74,75]. Moreover, 6 items were informed by the validated Beverage and Snack Questionnaire, which was tested with a diverse group of children as approximately 45% were from minority populations [70], and it was used in a more recent study that evaluated the efficacy of a serious game on low-income urban public school children’s dietary behaviors [76]. A total of 3 items were internally created (related to assessing the intake of different types of water).

##### Child Anthropometric Measures

Height and weight of child participants were measured using standardized methods [77]. Height was measured to the nearest 1/8 inch using a digital stadiometer (SECA 264), with the participant fully erect, without shoes, feet together, head in the Frankfort plane, and at the end of a deep inhalation. Weight and body composition were measured using a body composition monitor (Tanita MC-780U) wearing lightweight clothes and without socks and shoes. Weight was measured to the nearest 0.2 lb. Height and weight were measured in duplicate and recorded. A third measurement was taken if there was any uncertainty on the accuracy of height or weight measurements (eg, if height measurements differed more than 0.5 inch). An average of the measurements was used for the BMI calculations. The Centers for Disease Control and Prevention BMI percentile calculator was used to determine BMI percentage [78]. If needed, the average height was rounded down to the nearest eighth of an inch, and the average weight was rounded down to the nearest quarter pound, to accommodate the calculator’s units of measurement.

##### Parent Feeding Practices

Parent participants completed a questionnaire that asked about multiple parental feeding practices, specifically including 6 questions related to environment (ie, I offer a second helping of vegetables to my child during meals at home), 4 related to involvement in purchasing/preparing food (ie, I allow my child to help prepare fruit and vegetable dishes for family meals), 7 related to encouragement (ie, I encourage my child to drink water drinks [unsweetened] before sugary beverages), 8 related to modeling (ie, I model drinking water for my child even if it is not my favorite), and 2 related to teaching about healthy food practices (ie, I discuss with my child why it’s important to eat fruits and vegetables.). The 27-item questionnaire was informed by the validated Comprehensive Feeding Practices Questionnaire [71], which has been used in previous studies with low-income Hispanic parents and African American fathers [79,80].

##### Home Food Environment

Parent participants completed a questionnaire related to the availability of fruits, vegetables, and water in their home and how often they store fruits, vegetables, and water in a place easily seen by their child. The questionnaire comprised 6 questions and was informed by the validated Home Environment survey [72].

#### Potential Confounders

Demographic factors such as age, gender, race/ethnicity, and whether the United States was the country of birth for both the child and parent were collected. Additional child measures included grade, technology use, physical activity, sedentary behavior, and perceived health. Parental measures also included marital status, education level, household income, household profile, Supplemental Nutrition Assistance Program participation, child participation in school breakfast and lunch program, and perceived health. These measures were collected at T1.

### Data Management

A manual of procedures, including protocols related to data collection and storage, was developed at the outset of the study and refined continuously with input from all study staff. Study staff involved in collecting data were trained in implementing all procedures. Data collection and management procedures were reviewed at study staff meetings throughout the intervention period to ensure that they were followed with fidelity and to also address any issues or barriers to implementation.

Data collected in this study includes both quantitative data (auto-generated website usage data, online questionnaires, and anthropometric measures) and qualitative data (interviews). To ensure generated data are reliable, valid, and usable, the study staff used validated questionnaire items (or questionnaire items informed by validated questionnaires) and best practices for questionnaire, interview, and anthropometric data collection. Quantitative data were downloaded in spreadsheet format at least twice weekly, and qualitative data were downloaded as audio files weekly. All data were uploaded to password-protected institutional servers. Data were checked regularly to ensure the accuracy of data capture. A data dictionary that includes original items, answer choices, scoring/coding of answers, scoring of scales, and examples was created to ensure that all project data are accurately and readily usable and to aid in data analysis.

### Data Analysis

#### Quantitative Data

Usage and usability of the Web-based tool, along with the feasibility of study implementation, will be assessed using descriptive analyses. As usage data are key to understanding technology-based behavioral intervention dose and also how participants engage with the Web-based tool itself [81], patterns of usage by children and parents/guardians will be described/calculated in multiple ways including as a binary variable by week (eg, did child/parent visit the website in week 1), as an ordered variable based on usage over 6 weeks (eg, high use, low use, and minimal use), or as a continuous variable measured as number of times visited over 6 weeks. Previous studies have similarly assessed patterns of usage when analyzing user engagement with a website or app in an intervention [82-85]. Both usage and usability data will also be used to stratify analysis to determine if there are any significant associations between individual demographic characteristics and health-related outcomes. These data will have high relevance for interpretation of outcome data and further inform refinement and enhancement of the intervention.

The changes in study outcomes within and between groups will be examined using mixed-models methodology with repeated assessments (T1, T2, T3, and T4), condition (experimental / comparison), and time by condition interaction. Both within- and between-group effect sizes will be calculated for all study measures to assess the magnitude of intervention effects overall and by potential moderators and inform subsequent larger RCTs. To control for multiple comparisons, *P* values will be evaluated based on the false discovery rate [86]. All analyses will be conducted using an intent-to-treat approach.

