### Sample Size

The sample size for this study was determined to reliably assess feasibility, acceptability, and preliminary efficacy of the intervention. We aimed to enroll a total sample size of 82 dyads (41 per group) [47,48], which allows for assessment of (1) intervention usage, usability, and feasibility/acceptability of study implementation and (2) both the within and between-group effect sizes as well as preliminary intervention efficacy based on mixed-models methodology (*d*=0.5, power=.80, alpha=.05, intraclass correlation coefficient=.6, 4 repeated measures), after taking into consideration estimated attrition of 20%. This sample size also allows to characterize potential sociodemographic moderators of the intervention as well as guide power calculations for a subsequent full-fledged RCT.

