### Limitations

This pilot study has limitations, which need to be considered. Initial recruitment challenges led to modifications in BMI eligibility criteria. In addition to overweight/obese children, healthy-weight children were also recruited. Not only could changes in BMI criteria dilute any anthropometric changes, but such recruitment challenges will also have implications for a larger scale randomized trial. Participants were recruited on a rolling basis over the course of 3 months; therefore, seasonality might bias various health-related behaviors, and thus our findings. The comparison group received similar health information (in non-narrative form), which may result in differences not being observed between groups. In addition, the comparison group (both child and parent) received 1 less text/email weekly reminder, which may influence tool usage, though this is likely to be minimal. Self-reported data from both the children and parents have been collected, which pose a validity risk, due to intentional/unintentional misreporting. However, our study design allows for children and parents to complete surveys at home as opposed to the study site with staff, which may contribute to decreased social desirability bias.

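### Within-group effect sizes are planned as measures of intervention effect and as input to the next trial, but a one-arm change also contains season and repeat testing

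*Protocol article*

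**What the plan says.** The Quantitative Data section specifies a mixed model with repeated assessments, "condition (experimental / comparison), and time by condition interaction". It then gives two kinds of effect size one shared purpose: "Both within- and between-group effect sizes will be calculated for all study measures to assess the magnitude of intervention effects overall", continuing "and by potential moderators and inform subsequent larger RCTs". P values are to be judged by the false discovery rate.

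The Sample Size section makes the same pairing. It lists within-group and between-group effect sizes together as quantities the sample is meant to support, under "power=.80, alpha=.05, intraclass correlation coefficient=.6, 4 repeated measures".

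On season, the Limitations section says that "seasonality might bias various health-related behaviors, and thus our findings" and attributes this to rolling recruitment. It does not say which comparison is exposed. Nothing in the article separates change over time within an arm from the effect of the intervention.

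**The concern.** The change within one arm is the sum of whatever the package did and whatever would have happened anyway. This design gives the second part several routes in:

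- **Season.** Every dyad moves from a late-summer or autumn baseline to a winter or early-spring follow-up, so time since baseline and calendar time run together within each arm.
- **Repeat testing.** Table 2 has children completing the knowledge, attitude and intake questionnaires four times, and parents completing theirs three times.
- **No untreated arm.** Comparison children also received tailored content, weekly goals and reminders, and their parents received newsletters, so that arm does not measure natural drift either.

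Two things are at stake. Both arms could appear to improve with no effect of either package, or a real gain could be hidden if the drift runs the other way. A planning effect size taken from within-group change would also mis-size the next trial. A within-group figure broken down by moderator has the same fault, since drift may differ between subgroups.

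**Working it through.** **Inputs from the article.** d = 0.5, power 0.80, alpha 0.05, intraclass correlation 0.6, four measures, 41 dyads per arm, 20% attrition (Sample Size); baselines August to November 2017, T3 at 6 weeks, T4 three months after the intervention ends (Study Design); trial concluded as of April 2018 (Results).

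**Assumed, not in the article.** A drift common to both arms of 0.1, 0.2 or 0.3 SD; equal correlation between visits; two-sided tests; normal approximation.

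**1. The plan's own figure.** For the mean of three post-baseline measures minus baseline, the variance per child is V = (1 − 0.6)(1 + 1/3) = 0.533. Then n per arm = 2V[(1.96 + 0.842)/0.5]² = 33.49, or 34. Inflating, 34 × 1.2 = 40.8, rounded up to 41 per arm and 82 in total. Dividing instead, 33.49/0.8 = 41.9, or 42 per arm and 84 in total. With 33 completers per arm (41 × 0.8 = 32.8), power is 0.794. The planned 82 is therefore recovered from a between-group contrast. The article does not say which contrast was used, and this point does not dispute the number.

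**2. Calendar.** Baselines from 1 August to 30 November 2017 put T3 at about 12 September 2017 to 11 January 2018, and T4 (13 weeks later) at about 12 December 2017 to 12 April 2018.

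**3. Where a shared drift goes.** Let δ be the common change, and τE and τC the effects of the comic and newsletter packages.
- Within the experimental arm: δ + τE
- Within the comparison arm: δ + τC
- Between arms: τE − τC

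If both effects are zero, each within-group effect size equals δ and the between-group one is zero.

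**4. Within-arm significance with no effect.** For one change score, SE = √[2(1 − 0.6)/33] = 0.156. The chance of nominal significance is Φ(δ/SE − 1.96) + Φ(−δ/SE − 1.96).

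| Shared drift δ (SD) | One given arm | At least one arm |
|---|---|---|
| 0 | 0.05 | 0.10 |
| 0.1 | 0.10 | 0.19 |
| 0.2 | 0.25 | 0.44 |
| 0.3 | 0.49 | 0.74 |

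The between-group test stays at 5% throughout.

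**5. Carrying the figure forward.** Suppose the true contrast is the planned 0.5 and the newsletters do nothing. The experimental arm's change then reads 0.6, 0.7 or 0.8. Required sample size goes as 1/d², so a trial sized on those values has (0.5/0.6)² = 0.69, (0.5/0.7)² = 0.51 or (0.5/0.8)² = 0.39 of the dyads it needs.

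**6. Regression to the mean.** The fruit/vegetable or water track was set from baseline intake and from child and parent self-efficacy. Simulating selection of the lower of two uncorrelated intakes at reliability 0.6 gives +0.22 SD for the targeted behaviour and −0.22 SD for the untargeted one. With self-efficacy given half the weight, the values are +0.16 and −0.16. Track assignment picks a behaviour, not the children, so across a whole arm the two parts cancel for fruit/vegetable intake and likewise for water. An artefact remains only in an analysis by track or of a pooled targeted behaviour.

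**The case against.** The strongest reply is that this is a matter of labelling in an exploratory pilot. The time-by-condition term already supplies the randomised contrast, diet is a secondary outcome, and season is disclosed. All of that is correct, and it limits the point to how within-group figures are named and used. It does not remove the point: the article states the purpose of those figures and sends them to later trials. The false discovery rate means that raw 5% significance is not the plan's criterion, so the probabilities above are illustrative. That adjustment deals with multiplicity, though, not with bias.

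It can also be said that the randomised contrast compares comic with newsletter, so only within-group change speaks to benefit over nothing. That explains the interest in it but does not make it causal.

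A reader might infer four stronger things that the article does not support:

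- **Regression to the mean inflates the planned diet outcomes.** It cancels in whole-arm outcomes, and the article defines no track-specific or pooled targeted outcome. Its size cannot be fixed either, because the track algorithm and weights are not given.
- **A change of survey setting distorts T1-to-T3 change, and the limitations text is wrong about it.** The article says "our study design allows for children and parents to complete surveys at home as opposed to the study site with staff" and separately describes "qualitative observations of child participants at T1 and T4 while completing questionnaires". These are compatible, and where T2 and T3 questionnaires were completed is not stated.
- **Within-group gains will decide progression.** The Conclusions tie a larger trial to acceptability, engagement and feasibility; the Abstract adds only potential to improve dietary behaviours.
- **Season biases the comparison between arms.** Allocation was concurrent, so a common shift largely cancels.

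**Conclusion.** The point holds for the interpretation and onward use of within-group effect sizes. The Quantitative Data section, supported by the Sample Size rationale, treats them as intervention effects, and in this design they also contain a shared seasonal shift and repeat testing, with no untreated arm to gauge either. The documents give no figure for that drift, in size or sign. If it were 0.1 to 0.3 SD, it would equal 20% to 60% of the planned d = 0.5 (0.1/0.5 to 0.3/0.5). With no effect at all, it would give a nominally significant within-arm change in about 10% to 49% of trials per arm. Those figures rest on the assumed drift, the plan's intraclass correlation of 0.6 and 33 completers per arm. The mixed model, the randomised comparison and the sample size of 82 are not called into question.

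**What to change.** - In Quantitative Data, and in the matching sentence of Sample Size, state that the intervention effect, overall and by moderator, and the effect size carried into the next trial come only from the between-group (time by condition) contrast. Say that this contrast estimates comic versus newsletter.
- Report within-group changes as descriptive before-after change with confidence intervals, and do not label them as intervention effects.
- In Limitations, add that a seasonal shift common to both arms affects within-group change and largely cancels in the concurrent randomised comparison.
- If outcomes are ever analysed by track or as a targeted behaviour, note that regression to the mean then adds to within-group change.

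The cost is wording and table labels, and the sponsor gives up within-arm effect claims. No new data are needed and the sample size does not change. The article reports that analysis was still under way, so the change concerns how results are labelled and used.

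### The quoted 80% power is unadjusted per-outcome power at alpha .05, not the power of the false discovery rate rule by which the P values will be judged

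*Protocol article*

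**What the plan says.** The Sample Size section sets a target of 82 dyads, 41 per group, after 20% attrition. One of its grounds is preliminary efficacy by mixed models with d=0.5 and "power=.80, alpha=.05, intraclass correlation coefficient=.6, 4 repeated measures". It names no outcome for this calculation.

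The Quantitative Data section under Data Analysis says that, to deal with multiple comparisons, P "values will be evaluated based on the false discovery rate". It gives no level q, does not say which tests form the family, and leaves no efficacy outcome outside the rule.

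The primary measures (usage, usability, feasibility) are to be analysed descriptively. Every outcome to which a power figure could apply is therefore secondary. Table 2 lists five secondary measures: dietary knowledge and attitudes, dietary intake, anthropometry, feeding practices and home food environment. None is ranked first.

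**The concern.** A power of .80 describes one test at a cutoff of .05. Under a false discovery rate rule the cutoff for any one outcome depends on how many outcomes are in the family and how many of them move. The two sections therefore describe different decision rules.

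What is at stake is how a null result will be read. The abstract makes a full trial depend partly on the tool looking like a possible way to improve dietary behaviours. A reader told that the pilot had 80% power for d=0.5 may take a non-significant adjusted intake result as evidence against an effect of that size. Under the stated rule such a result can be quite likely even when the effect is real.

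**Working it through.** **Inputs from the Sample Size section.** d=0.5, power .80, alpha .05 (two-sided assumed, since sidedness is not stated), intraclass correlation .6, four repeated measures, attrition 20%, 41 per group.

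**1. Reproducing the stated figure.** The contrast is not specified. The two-sided version that returns 82 after attrition is the mean of the three post-baseline values minus baseline. Its variance factor is (1 + 2×0.6)/3 + 1 − 2×0.6 = 0.5333.

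- n per group = 2 × 0.5333 × ((1.960 + 0.842)/0.5)² = 33.5, rounded up to 34.
- 34 × 1.2 = 40.8, so 41 per group and 82 in total. Dividing by 0.8 instead gives 43 per group, 86 in total.
- Completers at the planned size: 41 × 0.8 = 32.8 per group. Unadjusted power there is 79.2%.

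The plan's figure is thus recovered as one test at an unadjusted .05. The factor 0.5333 is a back-fit and does not stand in the article.

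**2. The cutoff under the rule.** Benjamini-Hochberg (assumed) with m tests rejects the k smallest P values at a cutoff of kq/m. At q=.05 that cutoff never exceeds .05, so power cannot exceed the unadjusted figure. At q=.10 it can.

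**3. Size of the family.** The article gives no count. A tally of the constructs in its Measures section is 6 knowledge and attitude constructs + 4 intake groups + 2 anthropometric measures (BMI, body composition) + 5 feeding-practice domains + 1 home environment = 18. Splitting or merging some of these gives 17 to 22. Families of 10 and 5 are shown as well; 5 is the number of secondary measures in Table 2.

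**4. Power under the rule.** With 33 completers per group the noncentrality is 0.5/√(2 × 0.5333/33) = 2.78. Average power per truly affected outcome, by simulation with independent outcomes:

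| Outcomes in family | q | 1 real | 9 real | all real |
|---|---|---|---|---|
| 18 | .05 | 42% | 65% | 76% |
| 18 | .10 | 52% | 77% | 86% |
| 10 | .05 | 50% | 75% | 76% |
| 5 | .05 | 59% | – | 76% |

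For 18 outcomes at q=.05, the values between are about 47% with two real effects, 51% with three and 54% with four. A correlation of .5 between outcomes lowers the figures by up to about 4 points.

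**5. Analytic check.** For a lone effect among 18 at q=.05 the cutoff is close to .05/18 = .0028 (z = 2.99). Power is Φ(2.78 − 2.99) = Φ(−0.21) = 42%, which agrees.

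**6. Number actually randomized.** With 89 dyads (44.5 per group on average) and 20% attrition, 35.6 per group remain. Unadjusted power becomes 82%. A lone effect among 18 at q=.05 has about 47%.

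**The case against.** The strongest case on the other side has four parts.

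- **The family and q are unknown.** An article often leaves them to the analysis plan, and a per-domain family would shrink the gap. This stands. It is why the result is a range and why 18 is only a tally. It does not remove the mismatch, because the article itself states both the .05 power basis and the false discovery rate rule.

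- **A lone effect is the worst case.** The tool is meant to move knowledge, self-efficacy, intention and intake together. This stands too. A reader might infer that a real d=0.5 effect on intake would more likely than not be missed. The documents do not support that in general: at the planned size and q=.05 it holds only for one or two real effects in a family as large as 18. With three real effects power is about one half, and in a family of 5 a lone effect has 59%.

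- **The simulation gives every outcome the same four-visit contrast.** Table 2 measures anthropometry only at T1 and T4, and the parent scales at T1, T3 and T4. The figures for several real effects are therefore illustrative and do not forecast this trial's outcomes.

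- **This is a pilot.** Its primary measures are descriptive, efficacy is called preliminary, the sample size also rests on feasibility, and effect sizes are reported whatever the P values. The closing Conclusions tie the larger trial to acceptability, engagement and feasibility. This limits the consequence. A reader might also infer that the trial is too small for its main purpose; nothing here shows that.

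**Conclusion.** The point holds as a mismatch between the stated power and the stated decision rule. The "power=.80, alpha=.05" figure is unadjusted per-outcome power. At the planned size and q=.05, power for d=0.5 under the rule is below 80% in every scenario run, from about 42% (one real effect among 18) to about 76% (all real). At q=.10 it runs from about 52% to 86% with 18 outcomes, passing 80% only when nearly all effects are real.

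These figures assume Benjamini-Hochberg, two-sided tests, about 33 completers per group, equal effects and a common contrast with the back-fitted variance factor. The estimates of effect size are not affected.

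A reader might also conclude that one intake outcome should simply be taken out of the false discovery rate family now. The article does not support that as a safe step. Allocation was revealed at T4, the trial ended in April 2018 and analysis is under way, so the choice could be post hoc. The targeted behaviour also differs by child (fruit and vegetables or water), and the article gives no common scale for the two tracks.

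**What to change.** - In the Sample Size section, say that .80 is unadjusted per-outcome power at a two-sided .05.
- State q and the family of tests, and give the power under that rule for one and for several real effects.
- Say that non-significant adjusted secondary results will be interpreted from effect sizes with confidence intervals, and will not be taken as evidence against d=0.5.
- Name a lead between-group intake contrast, tested at .05 outside the family, only if it can be defined on one scale across the fruit/vegetable and water tracks before anyone has seen group-level results. Otherwise reserve it for the full trial.

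No new data are needed. The cost is a few sentences and a less favourable stated power.
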